  - Total number of participants eligible for the intervention for each site (data collection by local PIs/research midwives at each trust)
  - Total number of participants who attend the intervention at each site (log to be maintained by the midwife facilitator for each intervention delivery session, to include number of participants in attendance at each session)
  - Location of intervention delivery for each session (log to be maintained by the midwife facilitator for each intervention delivery session, to include location)
  - Number of intervention sessions delivered (log to be maintained by the midwife facilitator for each intervention delivery session, each session to be numbered with unique ID)
  - Dates and times of each intervention session at each site (log to be maintained by the midwife facilitator for each intervention delivery session, to include date of session)

b) Piloting data collection procedures will include recruitment and retention of participants completing outcome measures, and data yield.

- Recruitment and retention: data will be collected on eligibility and consent rates, and retention of participants providing outcome measures at the scheduled time points. Recruitment and retention data will be collected at the levels of NHS Trust, midwives, and women. Data will be analysed to identify any systematic differences between those who agree to participate in the study and the general maternity population in the NHS Trusts recruited and thereby ascertain the extent of any participation bias. Data collection will include:
  - Number of midwives eligible to be approached to provide quantitative or qualitative data (data to be collected by the by local PIs/research midwives during recruitment process)
  - Number of pregnant women eligible to be approached to provide quantitative baseline data (data to be collected by the by local PIs/research midwives during recruitment process)
  - Number of pregnant women eligible to be approached to provide quantitative outcome data and qualitative process evaluation data (data to be collected by the by local PIs/research midwives during recruitment process)
  - Numbers of NHS Trusts, midwives and women approached/accepted/declined to participate in the study (data to be collected by the by local PIs/research midwives during recruitment process)
  - Number of NHS Trusts retained until the end of the study (log of recruitment and retention to be maintained by the CI)

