  - Number of midwives retained/data provided at each data collection time point until the end of the study (log of recruitment and retention to be maintained by the CI)
  - Number of women retained/data provided at each data collection time point until the end of the study (log of recruitment and retention to be maintained by the CI)
  - Characteristics of women eligible/recruited to ascertain the extent of any participant bias (recruited women will be asked to provide this information on a questionnaire; the local PIs/research midwives will have access to patient data from the electronic patient record system to provide anonymised pooled data for the recruitment time period for comparison)
- Data yield and data quality: information on data yield and quality will be used to identify any data collection methods which require further exploration (as part of the process evaluation), to refine the data collection tools and procedures where required (e.g. refine any questions that are confusing and therefore inconsistently complete in questionnaires, or change the time point for data collection if one time point results in consistently low yield or quality), and to inform decisions about what the primary and secondary outcomes should be for the definitive trial.
  - Data yield will be calculated by determining the percent of participants from whom data are collected at each time point (e.g. the percent of participants returning completed questionnaires; CI to assess)
  - Data quality will be descriptively assessed by determining the completeness (item response rates) and consistency of data for each participant at each time point, and over the duration of the study where data collection of the same outcome measures is required at multiple time points (e.g. number of questionnaire questions completed, consistency (where relevant) of specific questions being completed; CI to assess)

c) Piloting data collection for the planned analysis of a definitive trial will be carried out to ensure that the data being collected using the outcome measures are appropriate and sufficient. Additionally, the time and procedures required for data manipulation will be recorded to plan this workload for the definitive trial. This includes any data manipulation (e.g. coding) required to be carried out by the CI/statistician and by the local PIs/research midwives within the NHS Trusts (e.g. anonymising identifiable data). Data collection will include:

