| **All community midwives/cluster (intervention arm, 2 clusters)** |  | Consent, intervention delivery, completion of evaluation forms |  |  |  |  |  |  |  |
| **Random sample of 7 midwives/ cluster (intervention arm, 2 clusters)** |  |  | Consent, focus groups |  |  |  |  |  |  |
| **Convenience sample of 30 women/ cluster (all clusters)** |  |  |  |  | Consent women at 12 week scan and questionnaire data; follow up at 36 weeks, questionnaire data and weight measurement | Questionnaire data, weight measurement, case note audit | Questionnaire data, weight measurement | Questionnaire data, weight measurement | Questionnaire data, weight measurement |
| **Convenience sample of 10 recruited women/cluster (all clusters)** |  |  |  |  | Consent at 12 weeks, semi-structured interviews (3rd trimester) |  | Semi-structured interviews |  |  |

Study data collection details:

- Maternity electronic patient records: pregnant women’s characteristics including maternal age, BMI, ethnic group, parity, employment status, socio-economic status (determined by postcode anonymised by data linkage with index of multiple derivation data) will be retrieved from the electronic patient records for all eligible women in their 3^rd^ trimester during the recruitment period. Data will be anonymised and aggregated to compare with recruited women to determine any participation bias for each site.
- Women at 20 week scan – baseline only: eligible women will be approached and consented by a member of the research team (as per delegation log) before the intervention delivery to provide baseline data on their characteristics (including maternal age, gestation, BMI, ethnic group, parity, employment status, qualifications, postcode), questionnaire data. This is a one off data collection to compare how similar women are within and between sites before the midwives caring for them have received any intervention. The questionnaire data are:
  - Self-report of their midwives practice specific to the guideline recommendations (developed to reflect the midwives self-reported routine practice behaviour measurements)
  - Dietary Quality Score (DQS – validated in non-pregnancy with additional pregnancy and postnatal specific questions included)
  - Pregnancy Physical Activity Questionnaire (PPAQ – validated in pregnancy)
  - Psychosocial measures for understanding weight-related behaviours in pregnant women questionnaire (validated in pregnancy)

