- Eligible women at 12 week scan appointment: eligible women will be approached and consented to provide data on their characteristics (including maternal age, gestation, BMI, ethnic group, parity, employment status, postcode), questionnaire data, and 3^rd^ trimester weight measurements (to calculate weight change from booking). Some of the questionnaire data and weight measurements will be repeated postnatally (see table 2 for details of pregnancy and postnatal specific data collection). Recruited and consenting women’s case notes will be audited to determine feasibility of using this data source to inform the primary outcome, and to test the data collection form developed for the economic evaluation (phase 2 detailed in section 9.1.3). Case notes are retained by pregnant women antenatally and returned to the NHS Trust after discharge; therefore the audit will take place 3 months postnatally when case notes are returned.
- A subgroup of eligible women recruited to provide outcome data: women will be approached and consented by a member of the research team (as per delegation log) to take part in semi-structured interviews as part of the process evaluation. Interviews will take place during their last trimester of pregnancy, and again postnatally.

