| Identification of additional important information relating to midwives adherence to the guidelines not captured with above measures (e.g. detailed account of midwives successes/difficulties in adhering to the guidelines, behavioural constructs, issues with intervention delivery or translation to practice) | Focus groups with midwives | 1 month after training, 6 months after training |

| **Measure** | **Collection method** | **Timing of collection** |
| --- | --- | --- |
| **Women's behaviour** |  |  |
| Baseline characteristics at booking (BMI, parity, smoking status, age, ethnic group, post code [to determine socio-economic status using Index of Multiple Deprivation], employment, qualifications, stage of pregnancy at booking, past caesarean section, history of diabetes or gestational diabetes, alcohol consumption, maternal medical history [history of depression, thromboembolism, pre-existing essential hypertension]) | Electronic hospital records and maternity case notes (recorded at booking appointment) | After recruitment and consent - post-booking |
| Dietary and physical activity patterns | Women self-report validated questionnaires | Baseline, 3rd trimester, post-natal (3,6,9,12 months) |
| Engagement with referrals/support services for weight management | Women self-report questionnaires, attendance rates at existing weight management clinics (e.g. dietetics service etc) from hospital appointment system | Baseline, 3rd trimester, post-natal (3,6,9,12 months) |
| Costs incurred by women managing weight (gym membership, equipment purchased, attending ante-natal classes, family food costs, child care) | Qualitative interview | 3rd trimester, 6, 12 months post-natal |
| Additional appointments with community midwife relating specifically to weight management | Case note audit | After discharge |

| **Measure** | **Collection method** | **Timing of collection** |
| --- | --- | --- |
| **Women's short term health outcomes** |  |  |
| Gestational weight gain | Direct measurement | 3rd trimester |
| Weight retention | Direct measurement | 3,6,9,12 months post-natal |
| Psychosocial well-being measure | Self-report questionnaire | Baseline, 3rd trimester, post-natal (3,6,9,12 months) |
| Mode of delivery (spontaneous, induced, assisted vaginal, unassisted vaginal, elective caesarean, emergency caesarean, analgesia use) | Electronic patient records; case notes | After discharge |

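### The participation-bias comparison sets recruited women's questionnaire answers against electronic-record values for eligible women, so source differences, mainly in BMI, can be read as participation bias or hide it (minor)

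*Protocol*

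**What the plan says.** Under objective 1, part (b), section 9.1.1 plans to look for systematic differences between women who take part and the wider maternity population, and "thereby ascertain the extent of any participation bias". The item that specifies the data is headed "Characteristics of women eligible/recruited to ascertain the extent of any participant bias". It names a source for each side. For recruited women, "recruited women will be asked to provide this information on a questionnaire". For the comparator, "the local PIs/research midwives will have access to patient data from the electronic patient record system to provide anonymised pooled data" covering the recruitment period.

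The Study Data section keeps the same split. Age, BMI, ethnic group, parity, employment and socio-economic status of eligible women are retrieved from the electronic record: "Data will be anonymised and aggregated to compare with recruited women to determine any participation bias for each site". For the women followed up after the intervention, "eligible women will be approached and consented to provide data on their characteristics", and the list that follows again covers age, BMI, ethnic group, parity, employment and postcode.

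Sections 11.4 and 13.2 have research midwives screen each woman's electronic record for eligibility before approaching her. In Appendix 4, the women's baseline characteristics at booking have as their source "Electronic hospital records and maternity case notes (recorded at booking appointment"), collected after recruitment and consent.

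**The concern.** A participation-bias estimate is a difference between two groups and should reflect only who took part. Here the two groups also differ in how the values were obtained: a woman's own answer at a scan-based recruitment contact on one side, the entry in the maternity record on the other. The difference then contains two things that cannot be separated: selection, and the gap between questionnaire and record. The comparator is pooled and anonymised, so it cannot later be linked to individual questionnaires to separate them.

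Participation bias is a named output of objective 1 in a pilot meant to shape a definitive trial. A reporting artefact could be taken as a sign that recruitment missed part of the population, or a genuine shortfall could go unseen. The point concerns the source of the values only. Which eligible women are pooled is a separate question.

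**Working it through.** The protocol gives no figure to reproduce, so the check has two parts: what follows from the text alone, and an illustration under stated assumptions.

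**1. Sources side by side**

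| Place | Recruited women | Eligible women |
|---|---|---|
| 9.1.1(b) | Questionnaire | Pooled electronic record |
| Study Data | Provided by the woman after consent | Electronic record, aggregated by site |
| 11.4 and 13.2 | Record opened at screening, not named as a source for this comparison | Record opened at screening |

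**2. Algebra**

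Let Q be the questionnaire value and E the record value. Then

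observed difference = mean Q(recruited) − mean E(eligible)
= [mean E(recruited) − mean E(eligible)] + [mean Q(recruited) − mean E(recruited)].

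The first bracket is participation bias and the second is the source gap. Under fully representative recruitment the first bracket is 0 in expectation and the second remains. Masking follows too: a true difference of +1.0 kg/m² with a source gap of −1.0 gives 1.0 − 1.0 = 0. With record values on both sides the second bracket vanishes.

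**3. Illustration for BMI**

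From the protocol: 30 women per site (section 16.2) and booking BMI of at least 30 kg/m² (section 10.1). Assumed, because the protocol gives neither: record BMI = 30 plus an exponential excess with mean 4 or 5; questionnaire minus record is normal with the mean shown and SD 1.0 to 1.5; recruited women are a random sample of eligible women. The simulation counts how often the site difference exceeds 1.96 estimated standard errors.

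| Assumed mean shift (kg/m²) | Expected apparent difference | Sites beyond 1.96 SE |
|---|---|---|
| 0 | 0 | about 8% |
| −0.3 | −0.3 | 12% to 13% |
| −0.5 | −0.5 | 15% to 18% |
| −1.0 | −1.0 | 27% to 35% |
| −1.5 | −1.5 | 43% to just over 50% |

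The reference rate is about 8%, not 5%, because the assumed BMI distribution is skewed and n is 30. A second model (gamma excess, mean 5, SD 4.5; error SD 1; 95% t intervals) gives about 6%, 13%, 28% and 44% to 47% for shifts of 0, −0.5, −1.0 and −1.5. Record against record, the rate stays at its no-shift level in both models: about 8% in the first and 5% to 7% in the second.

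For scale, with error SD 1 the standard error of a site mean is √((4² + 1²)/30) = 0.75 to √((5² + 1²)/30) = 0.93 kg/m². A shift of −0.3 to −0.5 is below one standard error.

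**4. Illustration for a category such as employment**

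With prevalence p in the record, and sensitivity se and specificity sp of the questionnaire category against the record category, the apparent difference is p·se + (1 − p)(1 − sp) − p. The se and sp values are assumed.

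- p = 0.30, se = 0.95, sp = 0.85: 0.285 + 0.105 − 0.30 = +9 percentage points.
- p = 0.60, same values: 0.57 + 0.06 − 0.60 = +3 points.
- p = 0.30, se = sp = 0.95: 0.285 + 0.035 − 0.30 = +2 points.

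The result depends on prevalence and coding, and the protocol does not say that the two codings differ.

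**5. Would planned checks reveal it?**

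The data-quality checks in 9.1.1(b) cover item completeness and consistency of responses, including across time points. None compares a questionnaire answer with the same woman's record.

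**The case against.** The strongest reply is that the effect may be small and the output carries little weight. Section 16 makes all analysis descriptive, no threshold attaches to the participation-bias summary, and the pilot is not expected to give definitive results. Women hold their own case notes during pregnancy (Study Data section); if they copy BMI from them, the BMI gap shrinks towards zero. Age, parity and postcode should agree closely. Item completeness is to be reported, and a questionnaire BMI below 30 would be noticeable, since every recruited woman has a booking BMI of at least 30. All of this stands and limits the point to a minor one. The BMI signal is weak, though: under the assumptions above with error SD 1, 7% to 9% of women would report below 30 from random error alone, with no mean shift.

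Two stronger readings are tempting and are not supported.

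- A reader might infer that reporting error also enters the women's weight outcome, change from booking. Nothing in the protocol takes booking weight from a questionnaire. Eligibility rests on booking data in the electronic record, and the list of characteristics women provide is introduced as non-exhaustive.
- A reader might infer that Appendix 4 contradicts section 9.1.1(b) by naming records as the source. That appendix lists information for economic modelling and a definitive trial. Collecting a variable both ways is not a contradiction in a pilot. Its relevance here is that it shows record extraction is already foreseen.

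**Conclusion.** The point holds as a minor one. The mismatch of sources is explicit in section 9.1.1(b) and repeated in the Study Data section. Its consequence follows by algebra without any outside figure: the stated participation-bias result includes the questionnaire-record gap and can be created or cancelled by it. The exposed items are BMI and, possibly, employment or ethnic-group coding and unanswered items.

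The size is unknown. Under the assumed BMI models the apparent site difference equals the assumed shift, from 0 to −1.5 kg/m², and exceeds 1.96 standard errors in about 8% of sites at no shift and about 43% to just over 50% at −1.5. These rates gauge how visible an artefact would be. They are not error rates of any planned test, because none is planned.

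**What to change.** In section 9.1.1(b), replace the questionnaire source for this comparison with wording such as: for consented women, age, booking BMI, ethnic group, parity, employment and postcode-derived deprivation are taken from the same electronic patient record, with the same coding, as the pooled data for eligible women. Make the matching statement in the Study Data section. Keep the questionnaire for items the record does not hold, such as qualifications. Where both sources exist, report their agreement as a data-quality result, which is useful to the pilot in its own right.

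The cost is small. Research midwives already open each woman's record at screening. The added work is copying six fields per consented woman under her study ID (30 × 6 = 180 fields per site for the follow-up sample) and confirming that the consent wording covers it.

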# Participants

The intervention and control participants will be community midwives, and any hospital-based midwives in the pilot sites with a specific maternal obesity or weight management role (e.g. public health midwife). The intervention aims to recruit all eligible midwives in the intervention arm to receive the intervention. This is due to the nature of shared care between community midwives meaning that any one pregnant woman might see a different community midwife from the team at each antenatal visit. If all midwives receive the intervention, this should increase consistency of advice and support for women who may receive care from a team of midwives. All midwives receiving the intervention will be asked to complete evaluation forms as part of the process evaluation. A further random subgroup of midwives from all participating Trusts will be selected to provide specific outcome and process evaluation data for the pilot. The study setting will be in the community where midwives practice. The intervention will be delivered in a training environment dependent on local availability for the pilot site communities (e.g. hospital academic centre, community NHS training facilities). The pilot study will take place in the North East of England.

Outcome measures will also be collected from eligible pregnant women (followed up postnatal), although these women will not receive the research intervention (midwifery training). For the purposes of this study, these women are also considered to be participants.

10.1 Inclusion criteria

- Midwives:
  - Midwives who have provided written informed consent for participation in the study prior to any study specific procedures
  - Community midwife role
  - Hospital-based midwife with a specific maternal obesity or weight management role
- Pregnant women:
  - Pregnant women who have provided written informed consent for participation in the study prior to any study specific procedures
  - Booking body mass index ≥30kg/m^2^ (proxy measure for pre-pregnancy BMI)
  - Age ≥ 18 years (teenage pregnancies require specific nutritional support)
  - Singleton pregnancies (multiple pregnancies require specific nutritional support)
  - Women who have had their 12 week ultrasound scan and their pregnancy has progressed beyond the high risk period for miscarriage

10.2 Exclusion criteria

- Midwives:
  - Hospital-based midwives without a specific maternal obesity or weight management role
  - Non-midwifery health professionals
- Pregnant women
  - Pregnant women with a medical condition other than obesity which requires them to receive specialist weight management advice for that condition (e.g. women with pre-gestational diabetes who are attending a specialist antenatal diabetes clinic, pregnant women who have had bariatric surgery (e.g. gastric band or bypass) and require specialist nutritional support)
  - Pregnant women with substance misuse or known cause for concern (e.g. domestic violence)

- Inability to speak/read English is an exclusion criteria for both midwives (to whom it is not expected to apply) and pregnant women. This is due to the questionnaire nature of the data collection and lack of validation in non-English language. Further feasibility work will be carried out with NHS Trusts who provide antenatal care for a high proportion of women from Black and Minority Ethnic (BME) Groups to assess transferability of the intervention to populations with more varied ethnic diversity than the North East of England to further inform intervention development prior to a definitive trial. This feasibility work will require a stand-alone protocol and will be subject to a separate ethics application.

